## Abstract

**Background:**

Following discharge, it is crucial for patients to transfer intentions and action plans from inpatient rehabilitation into everyday life. This ensures their reintegration into social and working life and prevents economic costs due to sick leave or reduced earning capacity pension. However, most established aftercare programs do not specifically address occupational problems or challenges during occupational measures such as graded return to work. The aim of this study is to evaluate the efficacy of the low-threshold online self-help intervention *marena* (Meine Arbeitsbezogene Reha-Nachsorge - My Work-related Rehabilitation Aftercare) to support return to work.

**Methods:**

A two-arm randomized-controlled-trial (RCT) will be conducted. A total of *N* = 400 rehabilitation inpatients across different indication areas (psychosomatic, orthopedic, or cardiologic) aged 18 to 65 years with a planned return to work after medical rehabilitation, have a heightened social-medical risk and private internet access and are insured with the German Pension insurance or statutory health insurance, will be recruited in four medical and psychosomatic clinics in Germany. Participants will be allocated to either the intervention (IG) or the control group (CG). In a stepped-care model, participants of the IG will receive access to the non-guided internet- and mobile-based intervention *marena* (IG subgroup 1) or *marena* in combination with *GSA-Online plus* (IG subgroup 2), a guided psychodynamic internet-based intervention that has proven effective in two trials regarding occupational and health objectives. Based on a priori defined indication criteria, clinic staff will recommend either IG subgroup 1 or IG subgroup 2. The CG will receive optimized treatment as usual with access to a survey feature within *marena*. The primary outcome will be work status after 6 months (T2) and 12 months (T4). The endpoint at 12 months (T4) after discharge from inpatient rehabilitation will be considered as secondary endpoint. Work status is defined as positive if the participant is working and has ≤ 6 weeks of sick leave at T2 and ≤ 12 weeks of sick leave at T4. Secondary outcomes include successful completion of graded return to work, successful application for benefits for participation in working life, current work ability, social-medical risk, subjective prognosis of future employment, quality of life, somatic symptoms, coping, social support, depression, anxiety, and psychosocial stress.

**Discussion:**

This study will contribute to the evidence concerning efficacy of online aftercare interventions. If proven efficacious, *marena* could provide an individualized and adaptable self-help approach to promote return to work following inpatient rehabilitation.

## Background

1

Medical rehabilitation, as defined by the German Pension Insurance, aims to maintain work ability partially or completely and to (re-)integrate patients with chronic illness or disability into social and working life (Deutsche Rentenversicherung Bund, 2022). In Germany, inpatient rehabilitation is considered when outpatient rehabilitation is not possible or sufficient. In the clinic, patients receive support in managing their illnesses or disabilities, are formally incapacitated to work, and are distanced from daily burdens (Linden, 2014). Promoting sustainable behavioral change, e.g., regarding stress management or daily physical activity, is central to inpatient rehabilitation.

Research indicates that successful transitions of insights and health-promoting strategies from rehabilitation into daily life and work can lead to sustained health improvements and is crucial to maintaining long-lasting effects of rehabilitation (Köpke, 2016). Incorporating these strategies into personal and professional life, however, is a challenge for many patients. Consequently, suitable aftercare following acute treatment is crucial to avoid long periods of illness and to secure long-term workability and employment (Köpke, 2016).

The German Pension Insurance Association offers multimodal (IRENA) and unimodal (Psy-RENA) face-to-face aftercare concepts that stabilize the results of inpatient treatment (Deutsche Rentenversicherung, 2023) and thus promote return to work. However, uptake is limited due to a lack of outpatient services, long travel distances and limited time due to professional or family obligations (Harfst et al., 2003; Sibold et al., 2011). Furthermore, established aftercare programs predominantly focus on the treatment of physical limitations (Huber et al., 2014; Schulz-Behrendt et al., 2017). Specific problem situations, such as high psychological stress, interpersonal conflicts, or the lack of support in the personal or work environment, which indicate a need for social, emotional, and personal support are often overlooked (Kobelt et al., 2011; Schulz-Behrendt et al., 2017). Important aspects, such as support in terms of goal orientation, coping with illness, and accepting transitional phases with lower income (Klaus et al., 2018) are not addressed sufficiently.

To meet the demands for aftercare services and provide support acknowledging the specific needs of patients, low-threshold internet-based aftercare interventions offer a promising addition to traditional face-to-face interventions. Given the rapid development and increased reliance on digital solutions during the COVID-19 pandemic, increased acceptance and uptake of digital health applications by patients can be expected (de Witte et al., 2020). Accordingly, internet-based aftercare interventions are increasingly incorporated into routine care.

Numerous studies and meta-analyses provide evidence for the efficacy and effectiveness of internet-based interventions in prevention, treatment, and aftercare for various mental disorders (Barak et al., 2008; Sander et al., 2016; Andersson et al., 2019) and the maintenance of treatment gains post-treatment (Hennemann et al., 2018; Kockler et al., 2021; Stavric et al., 2022), although outcomes related to return to work are rarely studied.

The aftercare program *GSA-Online plus* (Healthy and Stress-Free at Work), a psychotherapeutically oriented guided online writing intervention for occupationally stressed rehabilitants, was evaluated in a previous randomized-controlled-trial (RCT). Participants of the intervention group (IG) reported a significantly more positive subjective prognosis of gainful employment (*p* = .018) compared to the active control group (CG). Additionally, measures of depression (*p* = .018), anxiety (*p* = .025), and psychosocial stressors (*p* = .015) decreased in the IG from baseline to follow-up, while corresponding scores increased in the CG (Zwerenz et al., 2017).

In an implementation study in a routine care setting, *GSA-Online plus* was prescribed significantly less often than expected (Zwerenz et al., 2019). We argued that the low referral rate may be due to *GSA-Online plus* focusing specifically on the psychological comorbidity. Interventions providing more general support with a practical focus on social work may be of greater benefit to the diverse target population and better fit the multidisciplinary treatment approach that is a main characteristic of inpatient medical rehabilitation in Germany (Zwerenz et al., 2019).

Therefore, the present study aims to develop and evaluate a low-threshold internet- and mobile-based tool for individualized return to work planning which provides support for a larger group of patients. The self-guided progressive web-app *marena* (My Work-related Rehabilitation Aftercare) aims to support return to work after inpatient medical rehabilitation. The intervention provides rehabilitation patients with information on rehabilitation measures and common strategies known from inpatient rehabilitation. The intervention is designed to support the implementation of action plans and exercises in the patients' daily lives. While still in rehabilitation, users are encouraged to identify personal aftercare goals. Following discharge, *marena* provides weekly tasks to work on these goals and, if necessary, seek personal or professional support or revise aftercare goals. Additionally, based on information provided by the user, such as the end of medical rehabilitation, the first day at work after rehabilitation, or a reported event such as sickness during a graduated return to work measure, *marena* automatically and dynamically provides content and recommends actions relevant to the user's specific situation.

To meet patients' individual support needs, IG participants will be given access to the interventions in a stepped-care model. As the unguided *marena* intervention is expected to be meaningful and appropriate for all individuals fulfilling the inclusion criteria of the study, all participants assigned to the IG will have access to *marena*. Participants of the IG with a specific need for occupational-related treatment (assessed with the social medical risk index SIBAR and clinic staff recommendation) and a need for individual therapeutic guidance will have additional access to *GSA-Online plus*. Participants of the CG will only receive access to a survey feature within *marena.*

Participants with access to *GSA-Online plus* will be more likely to have an unfavorable occupational prognosis (e.g., increased risk of early retirement, longer periods of sick leave, and an increased burden of symptoms). However, through interacting with their online therapists in the guided *GSA-Online plus* intervention, participants may receive additional benefits compared to those who only have access to *marena*. Hence, participants may not differ significantly on the primary outcome of work status but may show differences on secondary outcomes. To control for baseline differences in the two experimental conditions, we will conduct exploratory evaluations concerning adherence, satisfaction, and efficacy.

Furthermore, we will examine personal and work related variables, which in previous research have shown an impact on return to work. These include work ability (Figueredo et al., 2020), physical well-being (Schmidt et al., 2011; Streibelt and Egner, 2013), social support (Etuknwa et al., 2019; Figueredo et al., 2020), depression and anxiety (Islam et al., 2014; Hesse et al., 2019; Figueredo et al., 2020; Techniker Krankenkasse, 2023), somatic symptoms (Brouwers et al., 2009; Momsen et al., 2014), and stress. Due to the central protective function of resilient coping against psychological crises, which is associated with functions important upon return to work, such as active problem solving, seeking social support, and higher perceived health competence, among others, we additionally include the assessment of resilient coping (Sinclair and Wallston, 2004). Furthermore, we will take a look at the subjective prognosis of gainful employment due to the predictive value on (early) retirement (Mittag and Raspe, 2003; Bürger and Deck, 2009), as well as the completion of graded return to work and benefits for participation in working life measures, both of which are frequently used in the German rehabilitation system and are supported by *marena*. Finally, we will ask participants to rate their satisfaction as well as the usability and helpfulness of the interventions.

It is hypothesized that participants in the IG (online self-help intervention *marena*) will report significantly higher levels of return to work (work status at the end of the intervention and 12 months after discharge from rehabilitation) compared to the optimized CG as primary outcome. Furthermore, we expect that participants in the IG will report significantly better work-related outcomes (successful completion of graded return to work, successful application for benefits for participation in working life, current work ability, subjective prognosis of gainful employment), quality of life, and resources (coping skills, social support), as well as significantly less distress (lower rates of social-medical risk index, somatic symptoms, depression, anxiety, and psychosocial stress as secondary outcomes). Additionally, the two IG subgroups (*marena* alone and *marena* in combination with *GSA-Online plus*) are further compared on an exploratory level with respect to the primary and secondary outcomes.

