Eligible rehabilitants will be personally informed in a group presentation by the clinic staff or members of the study team. Furthermore, they will be provided written study information and a study flyer with a link to the study homepage. Upon receipt of the signed informed consent, clinical staff will assess whether IG subgroup 1 or IG subgroup 2 is indicated and provide the study team with the recommendation for an intervention subgroup and data needed for enrollment. Table 1 provides a listing of the indication criteria for each subgroup. Indication criteria were defined based on the *GSA-Online plus* implementation study and the clinics' assessment of the expected support needed by patients. We anticipate that one-third of eligible participants will get a referral for *GSA-Online plus*. The study team will randomly assign participants to the IG or CG and assign IG participants to the recommended subgroup. After randomization, participants will receive an e-mail with initial data to log into the allocated interventions.

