### Randomization

2.3

Participants will be randomized to either IG or CG in a 3:1 ratio, stratified by rehabilitation center. Randomization lists with permuted blocks of variable lengths will be created. Upon enrollment of participants by the clinic staff, the study team will access the respective randomization list provided by an independent researcher not otherwise involved in the study. If a participant is allocated to the CG, this is entered within *marena*. If a participant is allocated to the IG, the subgroup recommended by the clinical staff is entered within *marena.* Participants will be informed about their group assignment in the registration e-mail. Due to the nature of the interventions, blinding of the group assignment is not possible.

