### Sample size

2.7

The sample size was determined a priori using SAS 9.4 software. A Power analysis based on a power of 0.80, two-sided testing, an alpha-rate of 5 %, and a randomization ratio of 3:1 was conducted. According to Bethge (2017), Odds Ratios of 3.49 (referring to Streibelt and Bethge, 2014) and 2.41 (in Bethge et al., 2011; overall in Streibelt and Bethge, 2014) were observed for work-related occupational rehabilitation programs versus medical rehabilitation with regard to work status 6 months after discharge from rehabilitation. We plan more conservative with an Odds Ratio of 2.0. According to Bethge (2011), a work status rate of 51 % in the CG could be assumed. These assumptions resulted in a total sample size of *N* = 360 required for 80 % power and a binary logistic regression model to analyze the primary endpoint. When considering a correlation of ρ = 0.4 with indicators of specific occupational problems (at least 3-months of incapacity to work before rehabilitation, unemployment at the time of application, and the socio-medical assessment of limited performance in the last occupational activity; see also Bethge, 2017), the sample size can be reduced by ρ2 = 16 % to *N* = 320, due to the reduction of total variance through the explained variance of the covariates. Based on an estimated dropout rate of 20 % at the follow-up assessments T1 (at the end of the *GSA-Online plus* intervention) and T2 (at the end of the *marena* intervention) we plan to randomize *N* = 400 patients.

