### Limitations

3.2

First, we emphasize that there is no randomization between the two IG subgroups, as recommendations are made by the clinic staff. Therefore, selection bias may limit the generalizability of the results. To reduce bias, standardized training and information materials are provided to ensure that the selection of participants is as objective as possible.

Second, due to the nature of the intervention, study participants will not be blinded. Participants in the CG, who will not have access to the full version of *marena*, will be aware when reading the consent form and attending the group presentation, fellow patients will have access to a more favorable version of the intervention. To mitigate this potential disincentive, we decided to use an optimized CG.

Third, it should also be noted that content in *marena* supports participants during a graded return to work, where participants remain on formal sick leave, and thus provides content that actively leads to inability to work. This may have a negative impact on the primary outcome work status. To reduce the risk of confounding of the criterion, we will not include work incapacity due to graded return to work in the outcome. Furthermore, including the duration of work incapacity in the screening instrument as well as the primary outcome may also confound the results.

Furthermore, a high dropout rate is to be expected, as internet-based interventions are typically subject to low adherence, especially in the CG. Therefore, multiple features of *marena* are designed to encourage compliance and questionnaire response, such as task reminders and questionnaires that are set to be active for a period of time and become mandatory close to the measurement points.

Last, the different functionality of *marena* on the Android (push notifications and e-mail) and iOS (e-mail only) operating systems may contribute to differences in user compliance. To control for this, the operating system used is included in the analysis as a control variable.

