### Conclusion

3.3

Patients returning to work following a medical rehabilitation face a diversity of challenges. Providing tangible and practicable advice regarding the pursuit of aftercare goals, aftercare programs/measures and benefits. If it proves to be effective, *marena* offers a highly adaptive, low-threshold approach to improve return to work in rehabilitation patients.

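### The primary contrast estimates a stepped-care offer but is worded as the effect of marena, and the planned efficacy comparison of the two intervention subgroups is confounded by indication

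*Protocol article*

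**What the plan says.** Study design (2.1) randomises patients 3:1 to IG or CG, stratified by centre only. All IG participants receive marena, and those judged to need it also receive GSA-Online plus. Section 2.2 anticipates a GSA-Online plus referral for one third of eligible participants.

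The order of events matters. After consent, "clinical staff will assess whether IG subgroup 1 or IG subgroup 2 is indicated and provide the study team with the recommendation", and only then does the study team randomise. Section 2.3 adds that for a patient allocated to the IG "the subgroup recommended by the clinical staff is entered within" marena. For a control it mentions only that the CG allocation is entered.

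The hypothesis at the end of the Background labels the IG as the self-help intervention marena, and the Conclusion says that, if effective, marena "offers a highly adaptive, low-threshold approach to improve return to work in rehabilitation patients". The two IG subgroups "are further compared on an exploratory level with respect to the primary and secondary outcomes", and Section 2.9 repeats subgroup as an exploratory factor. The Background expects GSA-Online plus users to have the less favourable occupational prognosis. Limitations (3.2) states that "there is no randomization between the two IG subgroups, as recommendations are made by the clinic staff" and gives limited generalizability through selection bias as the consequence. The fixed effects listed in Section 2.9 do not include the recommendation.

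**The concern.** There are two linked problems.

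First, the contrast and the claim do not match. IG versus CG answers whether offering the stepped package helps. It does not show whether marena alone helps, because part of the IG also receives a guided therapy that the Abstract describes as already proven effective. Nothing in the article compares marena alone with randomised controls.

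Second, subgroup 1 and subgroup 2 differ by the clinical judgement that separated them. A crude difference in work status mixes that judgement with any programme effect. This threatens internal validity, which is more than the loss of generalizability that Limitations names. The likely result is that the more intensive package looks useless or harmful when it is not, which could mislead decisions on whether to keep the guided step.

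A less biased analysis is nearly free. Because the recommendation precedes randomisation, comparing IG with CG among patients with the same recommendation is a randomised comparison.

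**Working it through.** **Inputs from the article.** Sample size (2.7): "A Power analysis based on a power of 0.80, two-sided testing", "an alpha-rate of 5" percent, "a randomization ratio of 3:1 was conducted"; OR 2.0; control rate 51%; dropout 20%; 400 randomised. Section 2.2: one third recommended for GSA-Online plus.

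**The plan's own figure.** The IG rate under OR 2.0 comes from odds 2 × 0.51/0.49 = 2.082, so p = 2.082/3.082 = 0.6755. The 3:1 pooled rate is (0.51 + 3 × 0.6755)/4 = 0.6341. With the pooled-variance two-proportion formula,

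n(CG) = [1.960·√(4/3 × 0.6341 × 0.3659) + 0.842·√(0.51 × 0.49 + 0.6755 × 0.3245/3)]² / 0.1655²
= (1.090 + 0.478)² / 0.0274 = 89.8, rounded up to 90.

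The total is 4 × 90 = 360, as stated. Also 320/0.8 = 400, as stated.

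**Bias of subgroup 2 versus subgroup 1.** Assumptions: true IG versus CG OR of 2.0 in both strata, overall control rate 51%, and a control rate in stratum 2 lower by d. The gap d is not in the article, so a range is shown. Stratum 2 control rate = 0.51 − 2d/3; stratum 1 control rate = that plus d. Each IG rate follows by doubling the odds.

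| d | CG rate, stratum 1 / 2 | IG rate, stratum 1 / 2 | OR, subgroup 2 vs 1 |
|---|---|---|---|
| 10 points | 0.543 / 0.443 | 0.704 / 0.614 | 0.67 |
| 20 points | 0.577 / 0.377 | 0.732 / 0.547 | 0.44 |
| 30 points | 0.610 / 0.310 | 0.758 / 0.473 | 0.29 |

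The within-IG OR equals the ratio of the control odds in the two strata, so it reflects prognosis only. IG versus CG within either stratum returns 2.0.

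**What the randomised strata can deliver** (one third recommended for GSA-Online plus, 20% dropout):

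- Recommended marena only: 400 × 2/3 = 267 randomised, about 200 vs 67; evaluable about 160 vs 53. Power for OR 2.0 is 58%; OR detectable with 80% power is about 2.5.
- Recommended marena plus GSA-Online plus: 133 randomised, about 100 vs 33; evaluable about 80 vs 27. Power is 34%; detectable OR is about 3.75.
- Standard error of the log OR at p = 0.5: √(1/(160 × 0.25) + 1/(53 × 0.25)) = 0.32 and √(1/(80 × 0.25) + 1/(27 × 0.25)) = 0.45.
- Treatment-by-recommendation interaction: about 24% power for a ratio of ORs of 2.
- If the recommended share is 25% to 50%, power falls from 63% to 47% in the first stratum and rises from 27% to 47% in the second.

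These powers apply the 51% control rate in each stratum, which is a simplification, and are unadjusted. With the 16% variance gain that the article assumes from covariates they become 66% and 39%.

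**The case against.** The primary test is randomised and valid, and the stepped-care design is stated openly in the Abstract, Methods and Discussion. The subgroup comparison is labelled exploratory, the Background predicts the prognostic gap, and Limitations concedes that the subgroups are not randomised. All of this stands, and it is why the point is not more severe. It does not give the reader a sound estimate for marena alone, and the exploratory label does not remove the confounding. The model in Section 2.9 includes SIBAR, which is one of the subgroup 2 criteria, but the other Table 1 criteria (stress about returning, conflict at work, need for guidance) are not among its terms, and the article does not say that the subgroup comparison uses this model.

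Three stronger readings are tempting but not supported.

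- **A reader might infer that the controls' recommendation is discarded.** Section 2.3 says only what is entered in the app. The recommendation goes to the study team and may already be on file.
- **A reader might infer that a positive primary result would probably be driven by GSA-Online plus.** Suppose marena does nothing and the GSA stratum has OR 3.49. The IG rate there is 0.784, the pooled IG rate is 2/3 × 0.51 + 1/3 × 0.784 = 0.601, and the pooled OR is 1.45. With 240 vs 80 evaluable, unadjusted power is about 30%, so this is possible but not likely. A pooled OR near 2 (1.99) needs a 60% share, against the article's one third. Moreover, OR 3.49 comes from work-related rehabilitation programmes; the article gives no work-status OR for GSA-Online plus.
- **A reader might infer that the stratum contrasts isolate GSA-Online plus.** They do not. Each estimates one package against control in its own population. The added effect would need randomisation among those recommended for it.

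**Conclusion.** The point holds as a should-fix. The primary IG versus CG test stands for the stepped-care offer; only its attribution to marena goes beyond the design. The subgroup 1 versus 2 efficacy comparison is confounded by a prognostic difference that the article itself expects. Under the assumed 10 to 30 point gap in control rates and equal true benefit, it would show an OR of about 0.67 to 0.29 where the stratum-specific truth is 2.0 in both. The direction rests on the article's own expectation of worse prognosis in subgroup 2. The size rests on the assumed gap and on no covariate adjustment, which might reduce it.

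**What to change.** 1. Confirm that the pre-randomisation recommendation is kept in the study database for all 400 patients, including controls.
2. Add it as a fixed effect in the primary model. Randomisation is stratified by centre only, so balance within recommendation strata is left to chance.
3. For efficacy outcomes, replace subgroup 1 versus subgroup 2 with exploratory IG versus CG estimates and 95% confidence intervals within each recommendation stratum, plus a treatment-by-recommendation interaction. Within-IG description of adherence and satisfaction can stay.
4. Word the primary conclusion as the effect of the stepped-care offer. Base any statement on marena alone on IG versus CG among patients recommended for subgroup 1.
5. In Limitations, name confounding by indication as a threat to internal validity.

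The cost is one data field already sent to the study team, one model term and changed wording, with no extra patients or assessments. The price in interpretation is imprecision: the stratum results are estimates with wide intervals, not tests to rely on, and a non-significant interaction would not show equal effects.
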